## Abstract

**Background:**

Depression, anxiety, and insomnia significantly impact global health and impose substantial health burdens worldwide. Conventional treatments including pharmacotherapy and psychotherapy face limitations in efficacy, side effects, and accessibility. Despite preliminary evidence suggesting the potential of Chinese herbal medicine (CHM) in managing these conditions, large-scale evaluations are lacking. This study aims to examine the effectiveness of CHM for the treatment of adults experiencing mild-to-moderate symptoms of depression, anxiety, and insomnia.

**Methods:**

This study will be a multicenter, pragmatic stepped-wedge cluster randomized trial. Districts will be randomized to receive the CHM intervention sequentially in four steps based on a computer-generated number, while control districts remain unexposed until their respective intervention phase. The intervention consists of a three-level stepped-care approach: Level 1 involves herbal tisane for mild symptoms, Level 2 offers standardized CHM for moderate symptoms or non-responders to Level 1, and Level 3 combines personalized CHM with psychotherapy for those not improved by Level 2. Symptom severity will be assessed using validated scales, Patient Health Questionnaire-9 for depression, Generalized Anxiety Disorder-7 for anxiety, and Insomnia Severity Index for insomnia, with primary outcomes measured at baseline, post-intervention, and follow-up. The study was approved by the Hong Kong Baptist University Research Ethics Committee (Approval No.: REC/22-23/0709).

**Discussion:**

This study will provide significant insights into the effectiveness of a stepped-care CHM intervention for alleviating depression, anxiety, and insomnia. The results could guide future decision-making regarding the integration of CHM into mainstream healthcare systems in Hong Kong and beyond.

**Trial registration:**

Chinese Clinical Trial Registry, ChiCTR2400083685, April 30, 2024,
https://www.chictr.org.cn/hvshowprojectEN.html?id=251238&v=1.0

AbbreviationsAEAdverse eventCHMChinese herbal medicineDMCData monitoring committeeDSM-IV
Diagnostic and Statistical Manual of Mental Disorders, fourth editionGAD-7General anxiety disorder-7I-BMS
Integrative body-mind-spiritICCIntra-cluster correlation coefficientISIInsomnia severity indexPHQ-9Patient health questionnaire-9PSS-10Perceived Stress ScaleRCTRandomized controlled trialSF-1212-item short form surveyTCMTraditional Chinese medicine

## 1. Introduction

### 1.1 Background and rationale

Mental and sleep disorders significantly impact global health, with depression, anxiety, and insomnia being the most prevalent and debilitating conditions.
^
1
^ Epidemiological studies indicate that depression is a leading cause of suicide,
^
2
^ while anxiety is the most common mental disorder across the globe.
^
3
^ Insomnia, often comorbid with both depression and anxiety, affects up to a third of the adult population worldwide.
^
4
^ The consequences of depression, anxiety, and insomnia extend beyond psychological health, exerting a drastic influence on physical well-being. Extensive research has indicated associations between the disorders and increased risks of developing physical comorbidities such as medically unexplained somatic symptoms,
^
5
^ cardiovascular diseases,
^
6–
8
^ diabetes,
^
9–
11
^ and cancer.
^
12,
13
^ Moreover, the global burden of mental disorders is escalating. According to the Global Burden of Diseases, Injuries, and Risk Factors Study of 2019,
^
14
^ depressive and anxiety disorders were the two most disabling mental disorders, both ranked among the top 25 leading causes of burden worldwide.
^
15
^ The pervasive impact of depression, anxiety, and insomnia present an urgent and nonnegligible challenge on the healthcare system.

According to clinical practice guidelines, pharmacotherapy and psychotherapy are the commonly recommended treatments for depression, anxiety and insomnia.
^
16–
19
^ However, recent evidence suggests that the efficacy of both treatments may have been overestimated.
^
20
^ Furthermore, pharmacotherapy presents major limitations, including delayed effects, non-responsiveness, risk of addiction, tolerance after long-term usage, and side effects.
^
21–
23
^ Psychotherapy can instead be limited by the unavailability of trained therapists and the high costs.
^
24
^ This is insufficient to combat the growing prevalence of mental and sleep disorders, especially in areas with a scarcity of mental health professionals. In Hong Kong, patients may need to wait for over two years for psychiatric consultations which last 6-8 minutes in average.
^
25
^ Moreover, up to three quarters of individuals suffering from mental disorders never seek medical help,
^
26
^ likely due to the social stigma and potential side effects attached to clinical treatments.
^
27–
29
^ Therefore, it is imperative to explore alternative treatments that are effective, accessible, and acceptable to meet the increasing needs of mental health care in the community.

Traditional Chinese medicine (TCM), including Chinese herbal medicine (CHM), acupuncture, dietary advice and exercise, etc., has been practiced for thousands of years for the treatment of depression, anxiety, and insomnia. Previous studies have reported the benefits of CHM in managing these conditions. For example, the widely used Xiao Yao decoction has been shown to elicit comparable benefits as antidepressants in alleviating depressive symptoms.
^
30
^ A recent meta-analysis reported that Xiao Yao decoction also improved insomnia symptoms.
^
31
^ Similarly, two randomized controlled trials (RCTs) have demonstrated the positive effects of Gui Pi and Huanglian Ejiao decoctions on anxiety symptoms.
^
32,
33
^ Importantly, patients treated with CHM were reported with fewer side effects compared to those taking antidepressants, anxiolytics, and sedatives.
^
30–
34
^ Furthermore, the holistic approach of TCM has been reported to be associated with less social stigma when compared to conventional psychological and psychiatric services.
^
35
^ This is particularly important as it could encourage more individuals to seek medical care without fear of being labelled or judged. Therefore, the implementation of CHM into conventional primary care settings may serve to promote help-seeking behavior from patients, while offering promising therapeutic benefits as well as reducing the burden of mental disorders on the healthcare system.

Although the effectiveness of CHM in alleviating sleep and mood disturbances has been previously reported, few studies examined the effectiveness of a stepped-care model for delivering CHM interventions. Evaluating such a model through traditional parallel randomized controlled trials (RCTs) could be limited by potential ethical concerns.
^
36
^ Instead, the stepped-wedge design presents a practical alternative for the evaluation, where the intervention is sequentially implemented across various time periods in a randomized manner.
^
37
^ This method has been successfully applied in various settings, including evaluating a sleep intervention using mentored behavioral and environmental restructuring to enhance sleep,
^
38
^ and a non-specialist delivered mental health intervention to improve common mental disorders and quality of life.
^
39
^ The stepped-wedge design not only facilitates continuous data collection at each intervention phase but also addresses ethical considerations by ensuring that all participants eventually receive the presumed beneficial intervention.
^
36
^ Additionally, this design allows for effective resource management when simultaneous intervention delivery is unfeasible and provides substantial analytical benefits by enabling participants to serve as their own controls, thus enhancing the ability to assess the impact of time on intervention efficacy.
^
36
^ Despite these benefits, the stepped-wedge design has not yet been applied to test the effectiveness of a stepped-care CHM intervention for depression, anxiety and insomnia.

### 1.2 Objectives

To address this gap, the current study employs a stepped-wedge cluster randomized trial design to evaluate the effectiveness of a stepped-care CHM intervention for the treatment of adults experiencing mild-to-moderate symptoms of depression, anxiety, and insomnia.

## 2. Methods

### 2.1 Trial design

This interventional study will be a multicenter, pragmatic, stepped-wedge, cluster randomized trial. Randomization will be carried out based on the 18 geographic districts in Hong Kong. The CHM intervention will be sequentially implemented in 4-6 districts per step according to a computer-generated random number while the remaining clusters will continue to stay unexposed to the intervention. After a 4-step exposure, all districts will receive the CHM intervention (
Figure 1). The study was approved by the Hong Kong Baptist University Research Ethics Committee (Approval No.: REC/22-23/0709) on April 8, 2024, and prospectively registered with the Chinese Clinical Trial Registry (ChiCTR2400083685) on April 30, 2024,
https://www.chictr.org.cn/hvshowprojectEN.html?id=251238&v=1.0. Recruitment started on May 1, 2024, and has already been completed. Data collection is expected to end in July 2025. The study is conducted according to the guidelines for good clinical practice (ICH/GCP) and the Declaration of Helsinki.
^
40
^ This protocol strictly adhered to the Standard Protocol Items: Recommendations for Interventional Trials (SPIRIT) 2013 statement (
**refer to data availability**).

**Figure 1. f1:**
[figure not shown]
Stepped-wedge study design. Note: This study will encompass 18 geographic districts in Hong Kong, with randomization occurring at the district level. The intervention will be rolled out sequentially to 4-6 districts at a time, based on a computer-generated random number. Meanwhile, the remaining districts will remain unexposed during the control period. After four steps of exposure, all districts will receive the intervention. Light grey boxes indicate the control period, while dark grey boxes represent the intervention period.

### 2.2 Study setting

The study will be conducted at three clinical centers, namely the Haven of Hope Hong Kong Baptist University Chinese Medicine Specialty Clinic, the Jockey Club Chinese Medicine Disease Prevention and Health Management Centre, and the Hong Kong Baptist University Mr. & [name] Yin Chinese Medicine Specialty Clinic and Good Clinical Practice Centre.

### 2.3 Eligibility criteria

**Inclusion criteria:** 1) Aged between 18 and 65 years; 2) Experiencing mild-to-moderate depression, anxiety, and insomnia, defined as a Patient Health Questionnaire-9 (PHQ-9) score between 5 and 19, a General Anxiety Disorder-7 (GAD-7) score between 5 and 14, or an Insomnia Severity Index (ISI) score between 8 and 21; 3) Understand and be able to follow written and oral instructions in Chinese to complete the assessment questionnaires; 4) Willing and able to provide informed consent.

**Exclusion criteria:** 1) History of alcohol and/or substance abuse disorder; 2) history of other major psychiatric or psychotic disorders (e.g., mania, schizophrenia, bipolar disorder, post-traumatic stress disorder or obsessive-compulsive disorder); 3) History of major neurologic disorder (e.g., Parkinson disease, Alzheimer disease or other dementia, brain tumor, seizure disorder or delirium episode); 4) Current active suicidal or self-injurious potential necessitating immediate treatment, or score ≥1 on the 9th item (suicidal ideation) in PHQ-9; 5) History of serious chronic illness, such as cancer, stroke, heart diseases, end-stage liver and kidney diseases; 6) Pregnant or lactating women; 7) Currently undergoing prescribed psychotropic medication, psychotherapy or TCM treatments for sleep and mood disturbances; 8) Allergic to CHM; and 9) Concurrent participation in other clinical trials.

### 2.4 Informed consent

Before participation, verbal and written information on the study will be provided. All individuals will undergo a detailed informed consent process where they are informed about the study’s procedures, risks, and benefits, ensuring their right to withdraw at any time. Written informed consent will be obtained before baseline outcome assessments.

### 2.5 Interventions

**2.5.1 Explanation for the choice of comparators**

The CHM intervention will be sequentially rolled out in a stepped wedge study design. In this design, each cluster contributes observations from both the unexposed (control) and the exposed (intervention) periods. This allows each cluster to serve as its own comparator over time. Additionally, comparisons are made between different clusters that receive the intervention at staggered times. This method ensures that every cluster acts as both a control and an intervention group, facilitating robust intra- and inter-cluster comparisons to assess the effectiveness of the CHM intervention.

**2.5.2 Intervention description**

In stepped-care models, the initial approach involves starting patients with a low intensity intervention. Progress is systematically monitored, and patients who do not adequately respond to the intervention can advance to a subsequent treatment of higher intensity or incorporate an additional treatment.
^
41
^ The stepped-care model has been proven to yield better clinical outcomes, enhanced efficiency in terms of resource use and cost.
^
42
^ Therefore, a stepped-care model will be employed to deliver the CHM interventions in the present study (
Figure 2).

**Figure 2. f2:**
[figure not shown]
Stepped-care intervention. Note: Mild symptoms: a PHQ-9 score ranging from 5 to 9, a GAD-7 score from 5 to 9, or an ISI score from 8 to 14; Moderate symptoms: a PHQ-9 score ranging from 10 to 19, a GAD-7 score from 10 to 14, or an ISI score from 15 to 21; Severe symptoms: a PHQ-9 score ranging from 20 to 27, a GAD-7 score from 15 to 21, or an ISI score from 22 to 28.

**Level 1: Herbal Tisane**

The Level 1 intervention, utilizing a low-intensity tisane including four herbs, is designed for participants with mild symptoms of depression, anxiety, and insomnia, defined by a PHQ-9 score ranging from 5 to 9, a GAD-7 score from 5 to 9, or an ISI score from 8 to 14. A Chinese medicine practitioner will prescribe the herbal tisane based on the participant’s main complaints. The Level 1 program includes three types of herbal tisanes for depression, anxiety, and insomnia respectively. Details of these tisanes are listed in
Table 1. The level 1 intervention will last for 6 weeks, where participants will be instructed to take the tisane twice daily. Upon completion of the six-week intervention, participants whose main complaints escalate to moderate level will be stepped up to receive the level 2 intervention, while other participants who present with mild/minimal symptoms will be followed up for another 6 weeks to examine the short-term effects of herbal tisane intervention.

**Table 1. T1:** The composition of the herbal tisane (Level 1 intervention).

	Latin Pharmaceutical Name	Chinese name	g/sachet
Depression Tisane	Curcumae Radix	Yujin	2
	Paeoniae Radix Alba	Baishao	3
	Fructus Tritici Levis	Fuxiaomai	4
	Acanthopanacis Senticosi Radix et Rhizoma Sue Caulis	Ciwujia	3
Anxiety Tisane	Nelumbinis Plumula	Lianzixin	0.3
	Paeoniae Radix Alba	Baishao	2
	Margaritifera Concha	Zhenzhumu	5
	Fructus Tritici Levis	Fuxiaomai	4
Insomnia Tisane	Coptidis Rhizoma	Huanglian	0.6
	Cinnamomi Cortex	Rougui	0.3
	Margaritifera Concha	Zhenzhumu	5
	Poria cum Radix Pini	Fushen	3

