**Level 2: Standardized CHM intervention**

The Level 2 intervention, employing a higher-intensity formula consisting of 5 to 11 herbs, is designed for participants experiencing moderate symptoms of depression, anxiety, and insomnia, defined by a PHQ-9 score ranging from 10 to 19, a GAD-7 score from 10 to 14, or an ISI score from 15 to 21. A Chinese medicine practitioner will prescribe the herbal formula based on the participant’s TCM syndrome. The Level 2 intervention includes three types of herbal formulas for excess syndrome, deficiency syndrome and deficiency-excess complex syndrome, respectively. The classification of these three syndromes will primarily rely on the clinical judgment of the Chinese medicine practitioner, who will consider the patients’ symptoms, signs, and other body constitutional characteristics. Importantly, all herbal formulas are standardized, which facilitates the evaluation of their effectiveness and allows for easy replication in future studies. Details of the three formulas are listed in
Table 2. The level 2 CHM intervention will last for 6 weeks, where participants will be instructed to take the herbal formula twice a day. Participants whose symptoms do not downgrade to mild level in their assessment score after level 2 intervention will be stepped up to receive the level 3 intervention, while other participants who downgrade to mild/minimal symptoms will be followed up for another 6 weeks to examine the short-term effects of the herbal formula intervention.

**Table 2. T2:** The composition of the herbal formulas (Level 2 intervention).

	Name	Ingredients	g/day
Excess syndrome	Jia Wei Xiao Yao San	Bupleuri Radix, Angelicae Sinensis Radix, Paeoniae Radix Alba, Atractylodis Macrocephalae Rhizoma, Poria, Glycyrrhizae Radix et Rhizoma, Moutan Cortex, Gardeniae Fructus	10
Deficiency syndrome	Gui Pi Tang	Ginseng Radix et Rhizoma, Jujubae Fructus, Ziziphi Spinosae Semen, Glycyrrhizae Radix et Rhizoma, Polygalae Radix, Zingiberis Rhizoma Recens, Angelicae Sinensis Radix, Atractylodis Macrocephalae Rhizoma, Poria cum Radix Pini, Astragali Radix, Longan Arillus	10
Deficiency-excess Complex syndrome	Huang Lian E Jiao Tang and Jiao Tai Wan	Coptidis Rhizoma, Scutellariae Radix, Paeoniae Radix Alba, Asini Corii Colla, Cinnamomi Cortex	10.3

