### 2.10 Sequence generation

Randomization of the sequence of initiation in 18 districts will be conducted 4 weeks prior to the commencement of study by an independent researcher (IR) not involved in assessment or delivery of the intervention. All 18 districts will receive no interventions in the first 4 weeks. After the first 4 weeks, 4-6 districts will initiate the stepped-care CMH intervention and this procedure continues at 4-week intervals, until all 18 districts cross over to the intervention phase.

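### No district is still in its control period at any 6-week follow-up or Level 3 post-treatment score, and the Level 2 follow-up is selected on the outcome

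*Protocol article*

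**What the plan says.** Section 2.10 fixes the calendar. For the lead-in, "All 18 districts will receive no interventions in the first 4 weeks"; then "this procedure continues at 4-week intervals, until all 18 districts cross over to the intervention phase". Section 2.1 gives the number of steps: "After a 4-step exposure, all districts will receive the CHM intervention".

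Section 2.5.2 fixes the treatment times. For Level 1, "The level 1 intervention will last for 6 weeks"; for Level 2, "The level 2 CHM intervention will last for 6 weeks". Level 3 has 8 weeks of herbal treatment, with counselling expected to finish within 12 weeks, then 12 weeks of follow-up. According to the Abstract, Level 3 is for those whom Level 2 did not improve.

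The same section decides who is followed up. At Level 1, participants who reach moderate severity step up; the rest "will be followed up for another 6 weeks to examine the short-term effects of herbal tisane intervention". At Level 2, those who do not come down to mild step up, while "other participants who downgrade to mild/minimal symptoms will be followed up for another 6 weeks".

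The Abstract counts follow-up among the primary-outcome times. Table 3 lists PHQ-9, GAD-7 and ISI as primary at every assessment, including A1_6w, A2_6w, A3_imd and A3_12w. Section 2.5.1 rests the evaluation on within-district comparison over time and on comparison between districts that start at different times. Section 2.15 names the Hussey-Hughes model.

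**The concern.** A stepped-wedge trial separates treatment from calendar time only while some clusters are exposed and others are not. Once all are exposed, the Hussey-Hughes model cannot tell treatment from period in those periods, unless it carries a constant effect forward from earlier ones. If follow-up and Level 3 scores all fall there, the randomisation gives them no concurrent comparison, and what is left is change from before to after treatment.

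The follow-up rule is a second problem. A score taken only in people who have just met a good-outcome criterion shows improvement even if treatment does nothing. Both problems concern readings that the protocol lists as primary. Reported without qualification, the Level 2 short-term result would be biased in favour of the intervention.

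**Working it through.** **Calendar.** Inputs: 4-week lead-in, 4-week steps (section 2.10), four steps (section 2.1). Sequence k crosses over at week 4k, so at weeks 4, 8, 12 and 16. The table adds the time from crossover to each score (section 2.5.2) and counts the sequences still unexposed. Enrolment is taken on the first day of the step.

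| Score | Weeks after crossover | Study week, sequences 1 to 4 | Sequences unexposed |
|---|---|---|---|
| A1_imd, or A2_imd on direct Level 2 entry | 6 | 10, 14, 18, 22 | 2, 1, 0, 0 |
| A1_6w, or A2_6w on direct Level 2 entry | 6 + 6 = 12 | 16, 20, 24, 28 | 0, 0, 0, 0 |
| A2_imd after Level 1 | 6 + 6 = 12 | 16, 20, 24, 28 | 0, 0, 0, 0 |
| A2_6w after Level 1 | 6 + 6 + 6 = 18 | 22, 26, 30, 34 | 0, 0, 0, 0 |
| A3_imd, direct Level 2 entry, 8-week course | 6 + 8 = 14 | 18, 22, 26, 30 | 0, 0, 0, 0 |
| A3_imd, direct Level 2 entry, 12-week counselling | 6 + 12 = 18 | 22, 26, 30, 34 | 0, 0, 0, 0 |
| A3_12w, earliest | 14 + 12 = 26 | 30, 34, 38, 42 | 0, 0, 0, 0 |

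Even for the 6-week score, sequences 3 and 4 have no concurrent control. With 4 to 6 districts per step, two sequences hold at least 4 + 4 = 8 districts and at most 18 - 8 = 10. So 8 to 10 of the 18 districts have no concurrently controlled end-of-treatment score.

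Table 3 ticks consent at the Level 3 baseline, but no text allows direct entry to Level 3. If it did, only sequence 1 after an 8-week course (4 + 8 = week 12) would have a sequence still unexposed.

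**Selection.** The documents give no score distribution, so these inputs are assumptions: whole-number PHQ-9 scores from a normal distribution, mean 7 to 11, SD 5, equal correlation of 0.6 to 0.8 between any two visits, and no treatment effect. Three visits were simulated: baseline, end of treatment, follow-up. The severity bands are the protocol's (mild 5 to 9, moderate 10 to 19), and selection means a score below 10 at the end of treatment.

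- Level 2: 17 to 43% of entrants qualify for follow-up. They show an apparent improvement of 0.37 to 0.65 SD, against 0.10 to 0.44 SD in all entrants. The latter is ordinary regression to the mean.
- The part due to selection is 0.65 - 0.44 = 0.21 SD at mean 7 and correlation 0.6, and 0.37 - 0.10 = 0.27 SD at mean 11 and correlation 0.8. No combination gave more than about 0.28. In points, 0.21 x 5 = 1.05 and 0.27 x 5 = 1.35. The planned effect of about 0.2 SD (section 2.8) is 0.2 x 5 = 1.0 point.
- Level 1: selection shifts the change by about 0.1 to 0.2 SD, but the followed-up group's apparent change runs only from about -0.1 to +0.1 SD, because entry in the mild range involves little regression downwards.

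**The case against.** - An all-exposed final period is normal in stepped-wedge trials, and the protocol nowhere says that follow-up or Level 3 results will be reported as randomised effects. Section 2.15 specifies mixed models and intention to treat, not an analysis of the followed-up subset, and the details may be in an analysis plan that is not shown. This stands as far as intention goes: a reader might infer that uncontrolled results will be claimed as trial effects, and the text does not show that. But an analysis plan cannot create unexposed districts or scores that the follow-up rule never collects, and the protocol does list these times as primary.
- A reader might infer that every Level 3 score and every follow-up lacks any untreated reading. That goes too far. The Level 3 baseline (A3_bs) can fall at week 10 or 14, when districts are still unexposed. Sequence 1's follow-up at week 16 can also coincide with sequence 4's own baseline, taken before herbs are prescribed (section 2.13). Later enrolment in sequence 4 moves some of its untreated baselines past week 16. These are readings from districts that are crossing over or have done so, not from districts in their control period.
- A reader might infer that both follow-ups are inflated. At Level 1, someone who enters mild and stays mild is followed up and only escalators leave, so the spurious improvement is roughly nil. Step-up there also depends on the main complaint, so selection on PHQ-9 is indirect for someone whose complaint is insomnia.
- Part of the raw Level 2 figure is regression to the mean that affects all entrants. This stands, and only the excess is attributed to selection here.
- Table 3 shows no separate control-period assessment apart from baseline. So even the 6-week comparison in sequences 1 and 2 relies on baseline scores in the unexposed districts.

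**Conclusion.** The concern holds in this form: no 6-week follow-up and no Level 3 post-treatment score is taken while a district is still in its control period. Follow-up starts at week 16, at best on the day of the last sequence's own pre-treatment baseline, and Level 3 post-treatment scores start at week 18. Only the end-of-treatment scores of sequences 1 and 2 overlap unexposed districts. This follows from the protocol's stated schedule alone.

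The Level 2 short-term effect is also selected on the outcome. Selection adds about 0.21 to 0.27 SD under no effect, as large as the effect the trial is planned on. That size depends on the assumed means, SD and correlations, whereas the direction follows from the rule for any positive correlation between visits. At Level 1 the follow-up group is restricted too, but without material apparent improvement.

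**What to change.** Recruitment is complete, so the calendar stays as it is. The changes are to analysis and wording.

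1. Limit the confirmatory stepped-wedge comparison to the score 6 weeks after start: A1_imd, or A2_imd for direct Level 2 entrants.
2. Report A1_6w, A2_6w, A3_imd and A3_12w as descriptive before-after results without concurrent control. The same applies to A2_imd reached through Level 1, which falls at week 16 or later.
3. Do not present the followed-up subset as the Level 2 short-term effect. Estimate later change with a mixed model that uses all available scores of everyone who started.
4. State the limit of that estimate. At 12 weeks after start, those who stayed at Level 1 have A1_6w, those stepped up from Level 1 have A2_imd, and direct Level 2 entrants who improved have A2_6w. Direct Level 2 entrants who step up to Level 3 have no score then; their next is A3_imd, 14 to 18 weeks after start. A week-12 estimate in everyone therefore rests on the model for this group, which is the one whose absence causes the Level 2 selection.

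The cost is that claims on durability and on Level 3 become weaker. No new data collection is needed.
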